### Secondary objectives

To determine the best instruments for measuring outcomes in a future trial by examining the quality, completeness and variability in the data.To estimate the treatment effect sizes and standard deviations for outcome measures to inform the sample size calculation for a large-scale RCT.To determine whether patients who are overweight/obese view computer-based attention trainings as acceptable and credible.To obtain information about patients’ willingness to undergo random allocation to ABMT, MT or waiting list for eight weeks.To evaluate the relationship between AB and eating behaviour.To identify AB modification after training and its association with symptom change.To compare eating behaviour and weight change between conditions before and after training.To identify potential additional underlying mechanisms of attention trainings related to reward processing and self-regulatory processing using neurocognitive tasks.

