#### Outcome measures

A range of outcome measures will be included with the aim of determining the most appropriate ones for a larger-scale RCT (based on effect sizes). The metric, timing and method of aggregation specifications for all outcome measures are described in the ‘Analyses’ section of this protocol. They are in accordance with Zarin et al. [38].

Clinical outcomes
Eating behaviour-related measures: BMI will be calculated measuring body weight and height (kg/m^2^) and body composition (primarily body fat percentage) will be assessed using a bioelectrical impedance scale (InBody S10). The Eating Disorder Examination Questionnaire (EDE-Q) [39] assesses specific psychopathology of eating disorders using a 36-item self-report format. The Power of Food Scale (PFS) [40] evaluates the psychological impact of the modern ‘obesogenic’ environment. Dietary Recall over 24 h will be used to assess the quality of participants’ diet. VAS scales will be used to measure hunger and craving. In addition, VAS scales for cue-elicited food cravings will be administered after the Food Challenge Task [41] (short films created from Marks & Spencer’s adverts showing palatable foods). The bogus taste test [42] will measure food consumption of highly palatable food (i.e. crisps, chocolates and soft sweets) after asking participants to rate the food items according to smell, taste and attractiveness for 10 min. The difference in grams before and after the taste test will indicate the total food intake;Mindfulness and mindful eating-related outcomes: the Mindful Eating Questionnaire (MEQ) [43] is a 28-item questionnaire which will be used to assess awareness, distraction, disinhibition of eating and emotional and external eating. The Mindful Awareness and Attention Scale (MAAS) [44] is a 15-item scale to assess core characteristics of mindfulness;Other symptomatology: the Depression, Anxiety and Stress- Scale (DAAS-21) [45] is a 21-item self-report questionnaire which aims to evaluate mood, anxiety and stress levels over the previous week. The 20 items related to state-anxiety of the State and Trait Anxiety Inventory (STAI) [46] questionnaire will be used. VAS scales will also be used to measure current mood, stress and anxiety levels.

Neurocognitive outcomes

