#### Post-treatment assessment

The post-treatment assessment will be conducted after eight training sessions and will include all the measures used in the baseline assessment (apart from demographic information). In addition, to control for confounding variables, participants will be asked to answer a questionnaire about acceptability and credibility of the training as well as involvement in other weight-control intervention (including other research) during the eight weeks of training. A member of the research team will carry out assessment sessions with participants and will check outcome measures for completeness to ensure data quality.

Participants in the ABMT group will be asked to return the tablet after completion of the study.

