#### Follow-up assessment

Four weeks after the last session (i.e. week 12), participants allocated to either ABMT or MT will be contacted via email and will be asked to complete an online version of the EDE-Q including a question on their current weight, the PFS and the MEQ.

For the waiting-list group, the above questionnaires will be sent to participants at the end of the eight weeks of online training in addition to a question related to training adherence and involvement in other weight-control programmes. Participants will be compensated with £50 for their time and effort after completion of the study.

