#### Clinical and cognitive outcomes

Analyses will follow the intention-to-treat principle. Quality, completeness and variability of the outcome measures will be determined by the use of descriptive statistical analyses and graphical methods. Group differences will be estimated using linear mixed effects regression models, controlling for the baseline level of the outcome and the strata variable used in the randomisation. The aim is not to determine significant group differences but to establish a suitably precise effect size for the primary outcome at the post-treatment assessment. This estimate will be used to guide the sample size of a future efficacy trial.

The size of the treatment effect on each outcome measure will be the difference in mean scores between conditions at post-treatment (eight weeks) and follow-up (12 weeks).

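### The in-session completeness check is likely to raise and compress item completeness of the in-person questionnaires, which weakens completeness as one of the criteria for choosing instruments

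*Protocol article*

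**What the plan says.** Four parts of the protocol article bear on this point.

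- **Secondary objectives.** The first is "To determine the best instruments for measuring outcomes in a future trial by examining the quality, completeness and variability in the data".
- **Outcome measures.** A range of measures is included so that the most suitable can be identified for the larger trial, and effect size is named there as the basis for the choice.
- **Post-treatment assessment.** A member of the research team carries out the assessment sessions and "will check outcome measures for completeness to ensure data quality".
- **Clinical and cognitive outcomes (Analyses).** "Quality, completeness and variability of the outcome measures will be determined by the use of descriptive statistical analyses and graphical methods". No distinction is drawn between completeness before and after the check.

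Under Follow-up assessment, participants in the two training groups are emailed at week 12 and "will be asked to complete an online version of the EDE-Q including a question on their current weight, the PFS and the MEQ". No staff check is stated for that step.

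**The concern.** Completeness and quality are properties the study sets out to measure in order to compare instruments. The session check is there to secure those same properties. A researcher who looks over a form while the participant is present, with the aim of ensuring quality, will usually point out skipped items and ask for them to be completed. The completeness then summarised is that of the instrument plus the check.

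What is at stake is limited but real. A questionnaire that people tend to leave partly blank (too long, unclear or intrusive) may look much like one they complete readily. That information is useful when planning a larger trial, particularly if collection there is less closely supervised. It cannot be recovered afterwards if the state of the form before prompting was not noted.

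**Working it through.** The article gives no completeness rates, so there is no stated figure to reproduce. The check has two parts: which measures the mechanism reaches, and how strongly it would act under stated assumptions.

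**1. Which measures are reached**

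- Table 1 and the Outcome measures section give six multi-item self-report questionnaires at both baseline and week 8: EDE-Q, PFS, MEQ, MAAS, DASS-21 and STAI. These are where a prompt could fill skipped items. The visual analogue scales and the 24-hour dietary recall are also self-reported and could be prompted in the same way.
- Body composition, the taste test, Food-ANT, the Visual Probe Task with eye tracking and the Food-Choice Task are also outcome measures. Lost eye-tracking data or a refused task is not obviously repaired by looking over a form.
- A missed visit or a withdrawal removes the whole measure, and the check does not change that.
- Going by the Follow-up assessment section, three of the six (EDE-Q, PFS, MEQ) are also completed online at week 12 without a stated check. The other three (MAAS, DASS-21, STAI) are scheduled only in person. The online data may therefore be informative for three questionnaires, but they offer no unprompted comparison with the other three.

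**2. How strongly the check could act**

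Let c be the proportion of forms complete without prompting and r the share of incomplete forms that the check repairs. Neither is given, so both are assumed, and r is taken as equal across questionnaires for simplicity.

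Observed completeness = 1 − (1 − c)(1 − r)

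Observed difference between two questionnaires = (c₁ − c₂)(1 − r)

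With c₁ = 95% and c₂ = 75%:

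| r | Questionnaire 1 | Questionnaire 2 | Difference (points) | Difference in forms out of 45 |
|---|---|---|---|---|
| 0 | 95% | 75% | 20 | 9.0 |
| 0.50 | 97.5% | 87.5% | 10 | 4.5 |
| 0.75 | 98.75% | 93.75% | 5 | 2.25 |
| 0.90 | 99.5% | 97.5% | 2 | 0.9 |
| 1 | 100% | 100% | 0 | 0 |

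With a narrower assumed spread, 98% against 85%, the 13-point difference becomes 13 × 0.5 = 6.5 points at r = 0.50, 13 × 0.25 = 3.25 at r = 0.75 and 13 × 0.1 = 1.3 at r = 0.90.

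The last column uses the planned total of 45 from the Sample size section. One form is 1/45 = 2.2 percentage points, so at 90% repair the remaining difference is about one form or less. The contrast can be lost in practice before repair is total, but it reaches zero only when every gap is repaired.

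**The case against.** The strongest reply is that the decisive step is inferred. The article says the measures are checked. It does not say that participants are prompted, that gaps are filled or that the first state of the form is discarded. A check could simply record what is missing and why. Whether missingness before the check is logged is the kind of operational detail that a condensed article leaves to the full protocol, which is not shown. This stands as a limit on certainty: the size of the effect is unknown and could be nil. It does not remove the tension, because the stated purpose of ensuring quality fits repair better than mere recording, and the analysis text does not say which completeness is meant.

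A reader might go further and infer that the study cannot meet its instrument-selection objective, or that differences between questionnaires fall to about zero. The article supports neither. Completeness is one of three criteria in the objective, and effect size is added elsewhere. Spread, floor and ceiling effects and effect size do not depend on whether a form was checked. A fall to zero needs complete repair on every instrument and no record of the earlier state, and neither is stated.

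A reader might also infer that the three questionnaires used online will be unfairly penalised. No passage pools week-8 with week-12 completeness, and all six are given in person at baseline and week 8, so a comparison under the same conditions exists. The article also does not say whether the online form permits skipped items. What remains is a reason to keep the two modes apart in reporting.

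Finally, if the larger trial used the same check, completeness under that check would be the relevant quantity. That is fair, but the article does not settle how the larger trial will collect its data, and having both figures serves either case.

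**Conclusion.** The point holds in a limited form. The article checks the measures for completeness in the session and then uses completeness to help choose among them. If the check leads to gaps being filled, item-level completeness of the in-person self-report questionnaires is raised and the differences between them are compressed. The amount is unknown. Under the assumed rates it ranges from no change with no repair, through halving at 50% repair, to about one form's difference or less at 90%.

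This rests on two assumptions: that the check results in correction, and that the state before prompting is not otherwise recorded. It weakens one selection criterion and leaves variability and effect size intact. It is a modest, inexpensive improvement to a stated secondary objective and does not threaten the trial's primary feasibility aims.

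**What to change.** Keep the check, and make four small additions.

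1. At each in-person assessment where the check is applied, record for each questionnaire the number of items missing as first handed in, before any prompt.
2. Use this first-submission figure as the measure of completeness when instruments are compared. Completeness after the check can be shown beside it.
3. Use the corrected data for the outcome analyses.
4. Report week-12 online completeness separately from in-person completeness, and state whether the online form permits skipped items.

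If the full protocol or the data-collection forms already provide for this, one sentence saying so is enough. The cost is one count per form and a completeness figure slightly less favourable than the one obtained after checking. The outcome data are unchanged.

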#### Follow-up assessment

Four weeks after the last session (i.e. week 12), participants allocated to either ABMT or MT will be contacted via email and will be asked to complete an online version of the EDE-Q including a question on their current weight, the PFS and the MEQ.

For the waiting-list group, the above questionnaires will be sent to participants at the end of the eight weeks of online training in addition to a question related to training adherence and involvement in other weight-control programmes. Participants will be compensated with £50 for their time and effort after completion of the study.

### Withdrawal of participants

One of the main outcome measures of this study is participant retention. We have a number of strategies to encourage continued participation of individuals (e.g. weekly email reminders and monetary compensation at the end of study). Should a patient decide to withdraw from the study, reason for withdrawal will be recorded and listed in the final report/associated publications. No further data will be collected from participants who decide to withdraw from the study.

### Biological specimens

No biological specimens will be collected.

#### Blinding

Due to the heterogeneity of the study conditions, blinding of participants will not be possible. For resource reasons and given the feasibility nature of the study, we will also not be able to blind outcome assessors. It is our opinion that this is unlikely to introduce bias as main outcome measures are objective, biological or implicit measures, such as BMI, body composition and assessing of computerised tasks, e.g. reaction times. However, the data analyst will be blinded.

### Analyses

#### Feasibility

Feasibility of the trial will be related to recruitment as well as retention rates at both post-assessment and follow-up. Acceptability of both trainings and effect sizes of treatment outcomes will also inform the feasibility for a larger-scale RCT.

#### Clinical and cognitive outcomes

Analyses will follow the intention-to-treat principle. Quality, completeness and variability of the outcome measures will be determined by the use of descriptive statistical analyses and graphical methods. Group differences will be estimated using linear mixed effects regression models, controlling for the baseline level of the outcome and the strata variable used in the randomisation. The aim is not to determine significant group differences but to establish a suitably precise effect size for the primary outcome at the post-treatment assessment. This estimate will be used to guide the sample size of a future efficacy trial.

The size of the treatment effect on each outcome measure will be the difference in mean scores between conditions at post-treatment (eight weeks) and follow-up (12 weeks).

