### Sample size

The sample size of this feasibility study is based on standard suggestions considering 12 participants per arm as reasonable sample size for a feasibility trial mainly because estimates of the standard deviation for normally distributed variables tend to stabilise around this size [34]. Considering a sample size of *n* = 36 and assuming the attrition to follow-up rate is a = 0.25, we strive for a sample size of *n* = 45, i.e. 15 participants per group (using an attrition correction factor of 1/(1-a)).

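### The promised precise effect size is not supported by 12 to 15 per arm, and the outcome it refers to is not identified, so it should not size the next trial

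*Protocol article*

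**What the plan says.** In the protocol article, Analyses, Clinical and cognitive outcomes, significance testing is disclaimed. The aim is instead to "establish a suitably precise effect size for the primary outcome at the post-treatment assessment". The next sentence gives its purpose: "This estimate will be used to guide the sample size of a future efficacy trial". The model is described as "linear mixed effects regression models, controlling for the baseline level of the outcome and the strata variable used in the randomisation".

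The Sample size section takes "12 participants per arm as reasonable sample size for a feasibility trial", because "estimates of the standard deviation for normally distributed variables tend to stabilise around this size". It gives no target width or confidence level for a between-group difference.

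The article does not say which outcome is meant:
- The Primary objective concerns recruitment, attendance and retention rates.
- Withdrawal of participants states: "One of the main outcome measures of this study is participant retention".
- Blinding gives BMI, body composition and computerised tasks as examples of main outcome measures.
- The Discussion paragraph of the Abstract speaks of primary outcome measures in the plural.
- Outcome measures says the most suitable measures for the larger trial will be determined from their effect sizes.

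**The concern.** The sample size argument concerns one quantity, the SD, while the analysis section promises precision for another, the treatment difference. The first does not deliver the second. An SD pooled over three arms can be usable at a size where the difference between two arms is still very uncertain.

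Required sample size varies with the inverse square of the assumed difference. If the future trial leans on a noisy estimate, its size inherits that noise, magnified. Choosing the future outcome by its observed effect size among many measures adds a bias: the measure that comes out on top tends to be one whose effect was overestimated by chance. A trial sized from that same estimate would tend to be too small.

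**Working it through.** **Inputs.** From Sample size: 12 completers per arm (36 in all), 15 randomised per arm (45 in all), and "assuming the attrition to follow-up rate is a = 0.25". From Clinical and cognitive outcomes: adjustment for baseline and for the randomisation factors (BMI class and gender, per Randomisation). The article gives no baseline-outcome correlation, so r is my assumption, varied from 0 to 0.95.

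**The plan's own figure.** The stated factor 1/(1 − a) gives 36/0.75 = 48, not 45; 45 is 36 × 1.25. With 45 randomised and 25% lost, 33.75 remain, or 11.25 per arm, slightly below the target of 12. That is a separate matter. It only means that the 12-per-arm figures below are slightly favourable under the plan's own attrition.

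**Half-width of one pairwise contrast.** In units of the raw SD:

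half-width = t(0.975; 3n − 6) × √(2/n) × √(1 − r²)

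The degrees of freedom allow for three arm means, baseline and two randomisation factors. By Table 1, body composition and the computerised tasks have a single post-baseline assessment, so for these the mixed model is close to an analysis of covariance and the formula is apt.

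- n = 12: t(30) = 2.042, √(2/12) = 0.408, product 0.834.
- n = 15: t(39) = 2.023, √(2/15) = 0.365, product 0.739.

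Multiplying by √(1 − r²):

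| r (assumed) | 12 per arm | 15 per arm |
|---|---|---|
| 0 | 0.83 | 0.74 |
| 0.5 | 0.72 | 0.64 |
| 0.7 | 0.60 | 0.53 |
| 0.9 | 0.36 | 0.32 |
| 0.95 | 0.26 | 0.23 |

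The last two rows are in raw SD. If the effect is standardised by the residual SD instead, the factor √(1 − r²) cancels and the half-width returns to 0.83 or 0.74 whatever r is.

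**What this means for planning.** Suppose 0.5 SD is observed with r = 0.5 and 12 per arm. The interval is 0.5 ± 0.72, about −0.2 to 1.2 SD. For a future two-arm comparison at 90% power and two-sided 5% (both assumed, no baseline adjustment), n per arm = 2 × (1.960 + 1.282)²/d². That is 85 at d = 0.5 and 15 at d = 1.2, with no finite size as d approaches zero, which lies inside the interval.

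As an illustrative benchmark, a half-width of 0.3 SD needs 2 × (1.96/0.3)² × (1 − r²) per arm: 86 at r = 0, 65 at r = 0.5 and 44 at r = 0.7.

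**The SD by comparison.** Pooled over 36 participants in three arms (33 degrees of freedom), the 95% limits are √(33/χ²) = 0.81 to 1.32 times the estimate. Since sample size varies with the SD squared, this alone moves a planned size by a factor of about 0.65 to 1.73 (0.807² to 1.316²). That is wide but workable.

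**The case against.** **Outcome left open by design.** Secondary objectives include choosing the best instruments, and Outcome measures says the candidates are still to be compared. A feasibility trial need not name a primary clinical outcome. This stands. A reader might infer that the plan has no primary outcome and must be made to choose one now. The documents do not support that: the article condenses protocol v.2.2, which is not shown, and the openness is deliberate. What remains is an inconsistency within the article, which refers to one primary outcome in the singular without saying which.

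**Precision depends on the outcome.** A reader might also take a half-width of roughly 0.6 to 0.8 SD as a fixed property of the design. It is not. It holds for r from 0 to about 0.7. BMI and body composition are among the examples given under Blinding, and for measures that stable r could be 0.9 or more, with half-widths of 0.23 to 0.36 raw SD. This also stands, and it is why r must be stated beside any figure.

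**The estimate only guides.** A third tempting reading is that the observed difference will be put mechanically into a formula and could yield any sample size. The article says the estimate will guide the calculation, and Secondary objectives already list SDs as an input. The article does not, however, say that the difference itself will come from anywhere other than the observed effect.

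None of these objections supplies a basis for calling the estimate suitably precise.

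**Conclusion.** The concern holds in a limited form. The sample size rationale supports estimation of an SD, not the precision claimed for a treatment difference. For one pairwise contrast the 95% half-width is 0.53 to 0.83 raw SD for r between 0 and 0.7, and 0.23 to 0.36 for r of 0.9 to 0.95, across 12 to 15 per arm. These figures rest on assumed values of r, a common SD, and randomisation factors that explain no further variance. Because the article does not identify the outcome, the applicable row of the table cannot be chosen.

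Small numbers are not the fault, and neither the feasibility objectives nor the disclaimer of significance testing is in question. The faults are the precision claim and the stated intention to size the next trial from this estimate, made worse by choosing the outcome on observed effect sizes. Correcting the text is advisable before the results are used for planning.

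**What to change.** In Clinical and cognitive outcomes:

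1. Replace the aim to "establish a suitably precise effect size for the primary outcome at the post-treatment assessment" with an aim to estimate, at post-treatment, *preliminary baseline-adjusted mean differences with 95% CIs for the candidate outcomes*.
2. State the expected half-width together with the assumed r, for example 0.72 SD at 12 per arm with r = 0.5.
3. Replace the sentence on guiding the future sample size with a statement that it will rest on a prespecified clinically important difference, the pooled SD and the baseline-outcome correlation estimated here, and not on the observed difference.

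Using an upper confidence limit for the SD is optional. A one-sided 80% limit multiplies the SD by 1.126 at 33 degrees of freedom, hence the planned size of the future trial by 1.126² = 1.27.

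The cost is a few sentences, one line of analysis for the correlation, and a less favourable statement of precision. This trial needs no extra participants, and the choice among candidate outcomes can stay open.
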